## Methods

### Study design

The effectiveness and fidelity of Houvast are investigated by means of a quasi-experimental research design with two groups and one baseline and two follow-up measurements (Figure 1). Both the intervention group and the control group (‘care as usual’) consist of Dutch services for homeless youth which deliver ambulatory and/or residential care. The services are randomly allocated to the intervention (*n* = 5) or control group (*n* = 5). Stratified randomization is used to ensure that services which deliver ambulant and/or residential care are equally distributed among each group. Randomization of homeless youths was not feasible since entire teams were trained prior to the baseline measurement in the strengths based method. Hence, a quasi-experimental research design is the best feasible design.

**Figure 1 F1:**
[figure not shown]
Flowchart of the randomization and measurement of the current study.

This study complies with the criteria for studies which have to be approved by an accredited Medical Review Ethics Committee region Arnhem-Nijmegen. Upon consultation, the Ethics Committee stated that due to the behavioural character of the intervention, the study was exempt from formal review (registration number 2011/260).

### Data collection

Measurements of primary and secondary outcomes are conducted among youths within the intervention group (*n* = 123) and the control group (*n* = 128) by means of three structured interviews. The first interview (T0) is conducted as soon as possible but within two weeks after the start of ambulant or residential care. Since the average duration of care delivered to homeless youths is three to six months, they are interviewed for a second time (T1) when services end care or when they have received care for a period of six months consecutively. The final follow-up interview (T2) takes place nine months after the first interview. In addition, professionals fill out an electronic questionnaire around T1 to obtain information about their perspective on the working relationship and the quality of life of a particular youth they provide care to. Based on the average number of homeless youths entering the participating services per year, the total period of the data collection is expected to be one year and nine months.

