### Selection and inclusion criteria

Services for homeless youth in the Netherlands who were identified through a web search and through our network were all approached for participation in the study. Inclusion criteria for services to participate in the study were:

1) targeted at delivering ambulant and/or residential care to homeless youth (not specifically at teenage mothers or in general to homeless adults);

2) provision of care to at least 15–20 homeless youths per year;

3) provision of care for an average period of at least three months consecutively (thus excluding emergency shelters).

Of the 35 services that were approached, 18 services attended an introduction meeting about the study. Finally, ten services agreed to participate in the study and eight services declined the opportunity to participate. Reasons for non-participation of services were:

1) not able to generate the necessary financial contribution (the funder requires a financial contribution for services to participate in the study, e.g. to cover expenses for training);

2) already having implemented other working methods;

3) already participating in other studies;

4) pending reorganization within services or organizations.

All youths who enter the service and receive either ambulant or residential care from professionals are included in the study. Exclusion criteria are:

1) youths still living with their parents while receiving ambulant care;

2) youths who end care within two weeks;

3) youths who cannot be interviewed within the first two weeks after entering the service.

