### Houvast

Youths in the experimental group receive care according to the Houvast method. Houvast aims at sustaining the recovery process of homeless youth by focusing on four conditional factors to achieve social quality: social inclusion, socio-economic security, social cohesion and social empowerment [30,38]. A trajectory comprises three parts, i.e., establishing a trusting working relationship and the setting of personal recovery goals based on a strength assessment, activities to support the personal recovery process of homeless youths and to achieve their goals, and evaluation and the ending or continuation of the trajectory. These parts are not free-standing but are interconnected, for instance, building a working relationship with youths and continuously updating the ‘strengths assessment’ and ‘recovery plan’ are important during the whole trajectory, as is constant reflection on activities and achievements. The strengths assessment and personal recovery plan are two primary tools in the strengths model that are meant to be executed in conjunction with each other. The strengths assessment allows youths and professionals to organize and make use of multiple strengths of youths in relation to resources in their living environment. After an estimation of the personal qualities of a particular youth is made, a personal recovery plan can help him or her to achieve their meaningful and important long term recovery goals step by step [30,31].

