### Measures among youths

#### Goals

To gain insight into the main goals homeless youths would like to attain, they are asked during the first interview to report three important personal goals for the next nine months. Next, for every goal a question regarding the importance of the goal and goal self-efficacy is administered which they can both answer on a 4-point Likert scale, varying from 1 (very unimportant or completely disagree) to 4 (very important or completely agree). Goal attainment is evaluated during the second and third interview by asking youths to what extent the earlier reported goals have been achieved. These questions are based on previous research on personal goals in relation to quality of life [46-48].

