Some limitations may be mentioned as well. First, due to the complex and unpredictable situation of homeless youth, it may be difficult to motivate them to participate in the follow-up interviews. Most youths leave the service within nine months and locating them to make an appointment for a final interview requires a large investment of researchers. By increasing the financial compensation for their time and effort to complete the interviews, they will hopefully remain motivated. Second, even though youths are interviewed for the first time during the first two weeks after entering the service, there is a small possibility that they were influenced in their scoring on the baseline measurement by whether they entered an experimental or a control service. We will inspect the baseline scores of both groups on significant differences in quality of life and the secondary outcomes, the last follow-up measurement will be conducted at nine months after baseline. Even though it is unique to follow homeless youths for this extensive period of time, a longer time span in which their recovery (or not) would have become more apparent would have been ideal. However, due to practical and financial constraints this was not feasible in the present study.

If the Houvast method proves to be effective in improving the quality of life of homeless youths, the study has strong practical relevance as the quality of work within services for homeless youth could be improved and more professionalized.

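### The baseline interview may fall up to two weeks into Houvast, so the personal goals used to score attainment, and baseline quality of life, can already depend on the arm

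*Protocol article*

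**What the plan says.** **Timing of T0.** The Data collection section states: "The first interview (T0) is conducted as soon as possible but within two weeks after the start of ambulant or residential care". The exclusion criteria apply the same limit, removing "youths who cannot be interviewed within the first two weeks after entering the service". Neither section requires T0 to come before the first Houvast contact.

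**Staff readiness.** The Study design section says that "entire teams were trained prior to the baseline measurement in the strengths based method".

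**Content of the method.** In the Houvast section, the first of the three parts of a trajectory is "establishing a trusting working relationship and the setting of personal recovery goals based on a strength assessment".

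**Goals as an outcome.** Attainment of personal goals is named in the second research question. In the Goals section, youths supply the yardstick themselves at T0: "they are asked during the first interview to report three important personal goals for the next nine months". Attainment at T1 and T2 is then measured by "asking youths to what extent the earlier reported goals have been achieved".

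**Acknowledgement.** The Discussion concedes a small possibility that youths were "influenced in their scoring on the baseline measurement by whether they entered an experimental or a control service". Its response is to inspect baseline quality of life and the secondary outcomes for significant differences between the groups. It does not mention the choice of goals.

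**The concern.** A baseline measurement should not be affected by the treatment. Here it is taken after allocation and possibly after treatment has begun. Two consequences follow, and they differ in kind.

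*Goal attainment.* The goals named at T0 define the outcome. If a youth in a Houvast service has already been through a strengths assessment and goal setting, the goals given to the interviewer may differ in kind or difficulty from those given in a control service. The arms would then be scored against different yardsticks. Covariate adjustment cannot repair this, because the goals are the target itself and not a prior value of the outcome.

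*Quality of life.* Any early benefit would sit in the T0 score. An analysis of change would subtract it, and a baseline-adjusted analysis would remove part of it. The primary comparison would be pulled toward no effect.

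**Working it through.** **Goals: the sections side by side**

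1. Teams can deliver Houvast from the first day of care (Study design).
2. The first part of Houvast includes personal goal setting (Houvast).
3. T0 may take place on any day up to day 14 (Data collection; exclusion criteria).
4. Some worker contact precedes T0 by design. Professionals approach the youth, the contact person gives more information and passes on contact details, and the researcher then schedules the interview (Procedure).
5. The goals named at T0 are the standard for attainment at T1 and T2 (Goals).

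It follows that the goals *can* depend on the arm. The article does not say how many youths have had a strengths assessment by T0, or how goals are handled early in usual care. No direction or size can be derived.

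**Quality of life: inputs**

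- Assumed effect 0.74, SD 1.48, two-sided α = 0.05, 80% power, 63 per group (Sample size and power calculation).
- Average duration of care three to six months, taken as 90 to 180 days (Data collection).
- Arm sizes 123 and 128; ICC 0.05; ten services.
- *Assumption:* a share f of the effect is present at T0. The article gives no value. Purely for illustration, f is set to elapsed time over duration of care, with every interview on day 14: 14/180 = 7.8% and 14/90 = 15.6%.

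**Step 1. The plan's own figure.** n = 2(1.96 + 0.8416)² × (1.48/0.74)² = 2 × 7.849 × 4 = 62.8, so 63 per group. This matches the article.

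**Step 2. Unadjusted change.** Contrast = 0.74(1 − f). Power = Φ(contrast/1.48 × √(63/2) − 1.96), before clustering.

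| f | Contrast | Power |
|---|---|---|
| 0 | 0.74 | 80% |
| 7.8% | 0.68 | 73% |
| 15.6% | 0.62 | 66% |

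**Step 3. Baseline-adjusted analysis.** *Assumption:* slope 0.5 and equal variances at T0 and follow-up. Contrast = 0.74(1 − 0.5f). Residual SD = 1.48 × √(1 − 0.25) = 1.28.

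| f | Contrast | Power |
|---|---|---|
| 0 | 0.74 | 90% |
| 7.8% | 0.71 | 88% |
| 15.6% | 0.68 | 85% |

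The loss is about 2 to 5 percentage points, against about 7 to 14 for the change score.

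**Step 4. What the baseline inspection could detect.** *Assumption:* baseline SD 1.48. The arm difference has SE = 1.48 × √(1/123 + 1/128) = 0.187, so only a difference above about 1.96 × 0.187 = 0.37 is significant. With about 25 youths per service the design effect is 1 + (25.1 − 1) × 0.05 = 2.2. The SE becomes 0.277 and the threshold about 0.54. The shifts in question are 0.74 × 7.8% = 0.06 and 0.74 × 15.6% = 0.12. The chance of a significant result is about 6 to 9% ignoring clustering and about 5 to 7% allowing for it, barely above the 5% expected with no shift.

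**The case against.** The protocol already asks for T0 as soon as possible, with two weeks as the outer limit, and the Procedure section shows why some delay cannot be avoided. The Discussion openly names the risk to baseline scores. An early benefit in quality of life works against Houvast, so it cannot manufacture a false claim on the primary outcome. The Analyses section plans a multilevel regression with adjustment, not a raw change score. All of this stands. It lowers the weight of the quality-of-life part, but it does not touch the choice of goals.

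Three stronger readings are tempting and are not supported.

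- *Goal attainment is biased in favour of Houvast.* A reader might infer that Houvast youths name smaller, supported steps while control youths name goals unaided. The Houvast section describes the goals as long term, with steps as the route to them; more ambitious goals would lower attainment. The Care as usual section leaves the control method to be described by questionnaire, so early goal setting there cannot be ruled out.
- *The strengths assessment has been done by T0.* No section dates it, and the parts of a trajectory are described as interconnected, with assessment updated throughout.
- *A fifth or more of the effect is lost.* Even benefit proportional to time, itself unsupported, gives at most 15.6%, and only if every interview is on day 14 of a 90-day stay. If T0 averaged day 7 (an assumption), the share would be 4 to 8% and power for a change score about 77 to 73%.

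**Conclusion.** The concern holds as a possibility that the stated timing rule leaves open, not as a demonstrated bias. The timing of T0, the opening content of Houvast and the definition of goal attainment together allow the yardstick of a named secondary outcome to be set after the intervention has begun. The article does not acknowledge this, and the direction and size are unknown.

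For quality of life the risk is disclosed, and an early benefit would bias toward no effect. The change-score contrast of 0.68 to 0.62 and power of 73 to 66% rest on an assumed share of 8 to 16%, ignore clustering, and apply only to an unadjusted change analysis.

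The planned baseline inspection does not settle either matter. A non-significant result rules out little, a significant one among ten allocated services could be chance, and goal attainment has no T0 value to inspect. This is a cheap improvement that protects a named outcome, not a flaw that undermines the trial.

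**What to change.** 1. In Data collection and Procedure, have the contact person refer promptly and the researcher book T0, where possible without delaying care, before the first strengths-assessment or recovery-plan session. In control services, the marker is the first care-plan session.
2. In both arms, record the days from entry to T0 and whether that session had taken place. Service staff should record session status, so that interviewers stay unaware of allocation. Report both items by arm.
3. Analyse quality of life adjusted for the baseline score.
4. Treat any analysis restricted to youths interviewed before that session as exploratory. The restriction selects on an event after allocation whose timing may differ by arm and service, so it is not an unbiased check.
5. Where goals were often named after that session, interpret goal attainment with that caveat.

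The cost is tighter scheduling of an interview already planned and two extra fields. The restricted analysis will be less precise and open to selection.

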### Selection and inclusion criteria

Services for homeless youth in the Netherlands who were identified through a web search and through our network were all approached for participation in the study. Inclusion criteria for services to participate in the study were:

1) targeted at delivering ambulant and/or residential care to homeless youth (not specifically at teenage mothers or in general to homeless adults);

2) provision of care to at least 15–20 homeless youths per year;

3) provision of care for an average period of at least three months consecutively (thus excluding emergency shelters).

Of the 35 services that were approached, 18 services attended an introduction meeting about the study. Finally, ten services agreed to participate in the study and eight services declined the opportunity to participate. Reasons for non-participation of services were:

1) not able to generate the necessary financial contribution (the funder requires a financial contribution for services to participate in the study, e.g. to cover expenses for training);

2) already having implemented other working methods;

3) already participating in other studies;

4) pending reorganization within services or organizations.

All youths who enter the service and receive either ambulant or residential care from professionals are included in the study. Exclusion criteria are:

1) youths still living with their parents while receiving ambulant care;

2) youths who end care within two weeks;

3) youths who cannot be interviewed within the first two weeks after entering the service.

### Procedure

Participating services were informed about the study by an information brochure and two working visits of the researchers to the service. During the first working visit with the (team) managers, information about the study and the service was exchanged and a contact person at the facility for the study was established. During the second working visit, the researcher informed the entire team (team manager and professionals) about the study by way of a one-hour interactive presentation.

Homeless youths are approached for participation in the study according to the following procedure: professionals approach all youths entering the service by providing leaflets and drawing attention to a poster with information about the study. If a youth agrees to participate the contact person gives him or her more extended information about the study and sends contact information about this potential participant to the researcher who subsequently schedules an interview appointment. The contact person is familiar with the inclusion and exclusion criteria. To protect confidentiality of the provided data, a unique code is assigned to each participant.

Preferably, all interviews take place at the site of the service and, if this is not possible, at a public place such as a library. After giving written informed consent, all instruments including self-report measures, are administered by means of face-to-face interviews by trained research assistants who are unaware of randomization of the service to the intervention or control group and have experience or affinity with working with vulnerable people, including homeless youths. Youths receive ten euro for participating in the first interview, 20 euro for the second interview and 35 euro for the third interview.

After homeless youths leave the service, locating them for making a second and third interview appointment is challenging because they have often moved to different parts of the country. Therefore, permission is asked in the informed consent at baseline to collect different sources of contact information such as e-mail addresses, phone numbers (e.g. from friends and family) and social media accounts. A protocol for contacting the respondents is established for both follow-up measurements. It consists of the following steps: calling, sending a text message, calling again, calling the contact person of the service, calling again, sending an e-mail, using social media and/or calling friends or family. Youths are excluded if no interview appointment could be made after accomplishing these steps (after four weeks). Every two to four weeks the researcher calls the contact person to verify if participants have left the service (and could be approached for a second or third interview) and to check if their contact information is still up to date.

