In this study several activities were carried out for the implementation of Houvast prior do the start of the data collection. Professionals in the experimental condition received a four day training provided by experienced trainers. Furthermore, two follow-up training days were organized for all trained professionals to further integrate the strengths based principles of Houvast and the fidelity criteria in their working methods, and to mutually exchange experiences about working with the Houvast intervention. In addition, internal coaches at the services within the intervention group were trained in getting familiar with the fundamental elements and competences of coaching to take responsibility for assuring and monitoring the implementation of Houvast and the model fidelity. Team leaders received a two and a half day training to learn what conditions need to be met within the organization in order to successfully implement Houvast. This is of particular importance because for a successful implementation of Houvast the organization and its management must adapt certain perspectives and practices. At the ‘pinnacle’ of the organization are the clients, and all organizational personnel are subservient to them. The managers are subservient to professionals. They need to be well grounded in the strengths based principles which are used by their professionals and to be able to integrate them in their policy [30,31].

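### Youths are recruited after service allocation by the services' own staff, so enrolment can differ by arm, and the planned baseline checks would often miss a moderate imbalance

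*Protocol article*

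**What the plan says.** Under Study design, ten services are randomised five to five. Individual randomisation is ruled out because "entire teams were trained prior to the baseline measurement in the strengths based method". The Houvast section confirms the order: "In this study several activities were carried out for the implementation of Houvast prior do the start of the data collection".

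Recruitment follows. Under Procedure, "professionals approach all youths entering the service by providing leaflets and drawing attention to a poster with information about the study". The service's contact person gives more information to a youth who agrees, then "sends contact information about this potential participant to the researcher who subsequently schedules an interview appointment". Of this person the article says: "The contact person is familiar with the inclusion and exclusion criteria".

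Selection and inclusion criteria counts every entrant who receives care as included. It then excludes, among others, youths whose care ends within two weeks and "youths who cannot be interviewed within the first two weeks after entering the service".

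Only the research assistants who interview are described as unaware of allocation. Two checks are planned. Analyses compares age, gender, education, nationality and ethnicity between arms. The Discussion adds an inspection of baseline quality of life and secondary outcomes. Analyses also adjusts for confounders, with gender, age, ethnicity, intellectual disability, duration of homelessness and model fidelity given as examples. The limitations mention that the service entered may colour baseline answers, but not that it may affect who is enrolled.

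**The concern.** Randomising services makes the youths who enter them comparable on average. It does not make the youths who are enrolled comparable if enrolment passes through people who know the allocation. Here the professionals make the first approach, and the contact person informs and refers. The speed of referral also affects whether a youth is interviewed inside the two-week limit. The other early exclusion, leaving care within two weeks, may itself respond to the care given, since Houvast starts by building a working relationship.

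Staff motivation may also differ by arm. The training, coaching and team-leader sessions took place only in Houvast services, and the Discussion reports that implementation has left staff keen. If one arm presents the study more warmly or refers engaged youths sooner, its sample starts with a different expected course. The comparison would then mix the effect of Houvast with the effect of selection. The interviewers' blinding comes too late to prevent this.

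**Working it through.** **1. The plan's own figure.** Sample size and power calculation gives a difference of 0.74, SD 1.48, 80% power and two-sided α = 0.05.

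n per group = 2 × (1.960 + 0.842)² × (1.48/0.74)² = 2 × 7.85 × 4 = 62.8, rounded up to 63. The stated 63 is reproduced, and the planned effect is 0.74/1.48 = 0.50 SD.

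**2. Can the baseline checks find an imbalance?** Inputs: 123 and 128 youths (Data collection), ten services, ICC 0.05 (Sample size and power calculation). I assume equal service sizes of 251/10 = 25.1, the same ICC for the baseline variable, and a normal approximation.

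- Design effect = 1 + (25.1 − 1) × 0.05 = 2.205.
- Effective sizes: 123/2.205 = 55.8 and 128/2.205 = 58.0.
- Standard error in SD units = √(1/55.8 + 1/58.0) = 0.187.
- Power ≈ Φ(d/0.187 − 1.96).

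| True imbalance d (SD, assumed) | Power, ICC 0.05 | Power, clustering ignored |
|---|---|---|
| 0.1 | 8% | 12% |
| 0.2 | 19% | 35% |
| 0.3 | 36% | 66% |
| 0.4 | 57% | 89% |
| 0.5 | 76% | 98% |

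The last column holds only if youths in the same service are independent. With only ten services, a t reference distribution would lower the middle column further.

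**3. What a missed imbalance could do.** If 0.2 SD carried through fully to the outcome, it would be 0.2 × 1.48 = 0.30 points, or 40% of 0.74. With the planned 178 youths at T1 (89 per arm), the design effect is 1 + (17.8 − 1) × 0.05 = 1.84 and the standard error is √(2 × 1.84/89) = 0.203 SD. An uncorrected bias of 0.2 SD would raise the two-sided type I error from 5% to about 17%.

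**4. How selection could produce such a shift (illustration only).** Let a fraction p of entrants be enrolled, and in one arm only let the propensity to be enrolled correlate ρ with later quality of life. The enrolled mean then shifts by ρ × φ(z_p)/p.

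- p = 0.6: φ/p = 0.644. For ρ = 0.1 to 0.3 the shift is 0.064 to 0.193 SD, or 13% to 39% of the 0.50 SD effect.
- p = 0.8: φ/p = 0.350. The shift is 0.035 to 0.105 SD, or 7% to 21%.

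Neither p nor ρ is in the article.

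**The case against.** The strongest reply is that the article contains safeguards. All entrants in both arms are to be approached, with leaflets and a poster. The two-week limit applies equally to both arms and keeps baseline close to entry. The arms will be compared at baseline, including on the primary outcome. The adjustment list goes beyond demographics to intellectual disability and duration of homelessness, and is open-ended. The design is openly called quasi-experimental, with a reason given. A condensed article may also leave an enrolment log to the full protocol.

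Much of this stands, and it limits the point. A reader might infer that differential selection cannot be detected, or that the trial will have no data to examine it. The documents do not support that: the baseline comparisons are data, and they have reasonable power against a large imbalance in a measured variable. A reader might also infer that no record of non-enrolled youths exists, or that control staff are stated to know their allocation. Neither is written. The article simply describes no such record. Prior training is documented only for the Houvast teams, and awareness in the control arm is a reasonable inference. That the contact person applies the eligibility criteria is likewise inferred.

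The reply does not remove the mechanism, which lies in the procedure as described. Approaching everyone leaves the manner of the approach and the speed of referral open. A uniform two-week rule can still act differently by arm. The Discussion itself allows that baseline scores may be influenced by the service entered, so an observed baseline difference could not be attributed clearly to selection.

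**Conclusion.** The point holds as a residual risk of recruitment bias that the described safeguards only partly cover. The planned checks see measured variables in enrolled youths only. They have about 19% power for an imbalance of 0.2 SD and 36% for 0.3 SD, assuming ICC 0.05 at baseline and equal service sizes. The procedure as described yields no count of entrants who were not approached, refused or were referred late, and the limitations do not name the issue.

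The actual bias cannot be sized. The figures of 7% to 39% of the planned effect rest on assumed enrolment fractions and correlations, and on selection in one arm only. Selection common to both arms would largely cancel. If the outcome is analysed as change from baseline, selection on a stable level of quality of life would partly cancel too. A reader might also infer that any bias favours Houvast, but nothing in the article fixes its direction. This warrants a change to the procedure. It does not invalidate the design, and no sample-size figure changes.

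**What to change.** Amend Selection and inclusion criteria, Procedure and the limitations in the Discussion as follows.

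1. At the call the researcher already makes every two to four weeks, the contact person also reports an anonymous consecutive list of all entrants: entry date, age, gender, ambulant or residential care, approached or not, and reason not enrolled.
2. The contact person passes on contact details only. The allocation-blind research assistant gives the fuller study information, from one script that is identical in both arms and does not name Houvast.
3. Youths missed by the two-week interview limit, and those leaving care within two weeks, are counted by service and arm.
4. Entrants, approached, refused and enrolled are reported by service and arm, and recruitment after allocation is listed as a limitation.

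This reduces part of the selection and makes more of it visible. The first approach stays with service staff. Inverse-probability weighting on the listed variables could be added as support only, because age, gender and setting cannot remove selection on engagement.

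The cost is modest. The calls and the blinded assistants already exist, but the calls now concern enrolled participants, so listing every entrant is a new, small task for contact persons.
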